### 2.4. Sample Size Calculation

The sample size was calculated using G*Power software according to the study of Charest et al. (2021) [23]. The study found d = 0.7012 for the Cohen’s effect size of tDCS on PSQI as the screening outcome of this study. Based on a 0.7012 effect size, bidirectional alpha of 0.05, and 80% test power, a minimum of 70 participants are required for this study. The sample will be increased by 20% to compensate for possible dropouts, and an overall sample of 84 participants will be included in this study.

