### 2.7. Primary Outcome Measures

#### 2.7.1. A-Sleep Monitoring

ActiGraph via synchronized wGT3X-BT software [25] will be used to objectively assess the physical activity parameters and sleep parameters. Actigraph is a valid and reliable tool for assessing sleep in healthy individuals [26]. The Actigraph sleep parameters are the following:i.Time in bed: the time between the ‘Lights Out’ and ‘Got Up’ times;ii.Actual sleep time: the total time spent sleeping according to the epoch-by-epoch wake or sleep categorization, excluding sleep latency and waking after sleep onset;iii.Wake after sleep onset: the amount of time a person spends awake, starting from when he or she first falls asleep to becoming fully awake and not attempting to go back to sleep;iv.Sleep efficiency: the ratio between the actual sleep time and time in bed.

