#### 2.7.2. B-Insomnia Severity Index (ISI)

The ISI will be used to quantify the severity of sleep impairments during the nights of the previous month [27]. ISI is a self-reported questionnaire that includes seven questions. The total score of the ISI ranges between 0 and 28, with a higher score indicating more severe insomnia.

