#### 2.7.3. C-Epworth Sleepiness Scale (ESS)

The ESS is used to assess the level of daytime sleepiness [28]. The ESS is a self-administered eight-item questionnaire that asks about the chance of falling asleep during performing eight daily activities on a scale from 0 to 3. The total score ranges from 0 to 24, with a higher score indicating worse daytime sleepiness.

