### 2.12. Statistical Analysis

The participants’ characteristics and outcome measures at baseline will be compared between the two groups using the Kruskal–Wallis test. Data will be screened for missing data, normality, and outliers. For variables that are not normally distributed, non-parametric tests will be used. The normally distributed data will be analyzed by repeated measures analysis of variance (ANOVA) to evaluate the therapeutic effect and changes between the two groups and within groups (group: sham vs. real tDCS) × (time: pre- vs. post-intervention vs. 1-month follow-up). Post hoc analysis will be applied to determine the exact groups with significant changes if significant findings appear. For the variables not normally distributed, we will use Friedmann’s test. The correlation between the changes in the Actigraph results with the athletes’ characteristics, DAAS-21, SF-12 pain, general health, role (emotional), and mental health domains at baseline will be analyzed by repeated measures linear regressions to understand the mechanism of improvement. The data will be analyzed using SPSS software, and a conservative *p*-value of 0.05 will be considered.

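### Six unranked primary outcomes are each tested at 0.05, called conservative, with no success rule: about a 17-26% chance of at least one false-positive primary if any one counts

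*Protocol article*

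**What the plan says.** Section 2.7 (Primary Outcome Measures) has three parts.

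- Section 2.7.1 opens its list with "The Actigraph sleep parameters are the following" and names four: time in bed, actual sleep time, wake after sleep onset and sleep efficiency. The last is defined from two of the others: "Sleep efficiency: the ratio between the actual sleep time and time in bed".
- Section 2.7.2 adds the ISI: "The ISI will be used to quantify the severity of sleep impairments".
- Section 2.7.3 adds the ESS: "The ESS is used to assess the level of daytime sleepiness".

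That makes six primary variables with no order among them. Section 2.5 measures them at baseline, directly after the intervention (T1) and one month later (T2), and does not say which visit decides.

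Section 2.12 plans, for each normally distributed variable, one repeated measures ANOVA of group by time over all three time points. Post hoc comparisons follow only after a significant finding. The section ends: "and a conservative *p*-value of 0.05 will be considered". The sample size in section 2.4 uses the same level for one outcome: "Based on a 0.7012 effect size, bidirectional alpha of 0.05, and 80% test power".

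**The concern.** Choosing the primary outcome and the error level is a protocol decision, and this protocol has made it: six primaries, each at 0.05. It then describes that level as conservative. A level of 0.05 is conventional for a single test. Applied separately to six primaries it is liberal, because each test adds its own chance of a false positive. A reader of section 2.12 would think false positives had been guarded against when the text shows no such guard.

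The hypothesis in the Introduction is only that stimulation could improve sleep in these athletes. With no stated success rule, a significant result on any of the six could be presented as confirming it.

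Time in bed makes this worse. The document gives it no direction of benefit, so a difference either way would be a primary result that neither supports nor contradicts the hypothesis. As the denominator of sleep efficiency, the same difference can also move a second primary.

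**Working it through.** **1. The plan's own figure.** The article states no familywise error rate. Its only figure tied to the 0.05 level is the sample size: "a minimum of 70 participants are required for this study". With d = 0.7012, two-sided 0.05, 80% power and 1:1 allocation:

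- the two-sample t-test needs 33 per arm (66 in total);
- the Wilcoxon-Mann-Whitney version (effective n = n × 3/π) needs 35 per arm, 70 in total, with power 0.806. This matches exactly, and 70 × 1.2 = 84 matches the recruitment target.

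So the 0.05 in section 2.4 is the level for one test of one outcome, and section 2.12 carries it unchanged to six primaries.

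**2. Independent tests.** The chance of at least one false positive among k independent tests at 0.05 is 1 − 0.95^k. For k = 6: 1 − 0.95^6 = 1 − 0.735 = 0.265, or 26.5%.

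**3. Correlated tests.** The actigraphy variables are linked by definition, so 26.5% is the independence value and not the expected one. The Discussion reports a low correlation between subjective and objective sleep measures but gives no figure. All correlations below are therefore assumptions, applied to six two-sided normal test statistics. The ISI-ESS correlation is varied over 0.3-0.5 and the subjective-objective correlation over 0-0.2.

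| Correlation among the four actigraphy variables | At least one false positive |
|---|---|
| 0.3 | 24-25% |
| 0.5 | 23-24% |
| 0.7 | 21% |
| 0.9 | 17-18% |

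If all six shared one common correlation, the rate would be 24.1% at 0.3, 20.8% at 0.5, 16.3% at 0.7 and 10.9% at 0.9. The last two do not fit a low subjective-objective correlation.

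**4. The planned test itself.** A null simulation of the group-by-time ANOVA used 35 per arm, three time points, sleep efficiency computed as sleep time over time in bed, and assumed standard deviations and correlations. At least one of the six interaction tests was significant in 20.8% of runs, inside the range in step 3.

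**5. Power cost of control.** Inputs: d = 0.7012 (the PSQI effect in section 2.4, assumed to apply to each outcome), 35 per arm, two-sided t-test with 68 degrees of freedom. The noncentrality is 0.7012 × √(35/2) = 2.93.

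| Level | Critical t | Power |
|---|---|---|
| 0.05 | 1.995 | 82.4% |
| 0.05/3 = 0.0167 (Holm's first step, three outcomes) | 2.455 | 68.3% |
| 0.05/6 = 0.0083 (Holm's first step, six outcomes) | 2.718 | 58.7% |

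**The case against.** Four points can be made for the plan.

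**The any-one-wins rule is not in the document.** The article speaks of assessing a set of sleep parameters, and outcome-by-outcome reporting fits the text as well. This stands as a condition: the rates above apply only if one significant primary is read as success. It does not remove the point, because the article sets no rule that would prevent that reading.

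**No adjustment is named, but none is excluded.** This is a condensed article, and a multiplicity procedure may sit in a full protocol or analysis plan that is not shown. That is fair, so the finding is not that adjustment is missing. It is that the article fixes six primaries at 0.05 and attaches a wrong description to that level. An unnamed post hoc correction might cover time points, but would not control error across outcomes.

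**The tests are not run visit by visit.** A reader might count six outcomes at two visits as 12 tests and quote 1 − 0.95^12 = 46%, or give a rate of 23-26% per visit. The document does not support this. It plans one group-by-time test per outcome, with post hoc comparisons only after significance. A range of 23-26% would also need independence or fairly weak correlation.

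**Two-sided significance in either direction holds for any outcome.** True. The difficulty with time in bed is narrower: no direction of benefit is stated, and it feeds another primary.

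**Conclusion.** The point holds in this form. Six primary outcomes are listed without ranking or a success rule, and each is tested at an ordinary 0.05 described as conservative, with no control across outcomes named. If any one significant primary is taken as support, the chance of at least one false-positive primary group-by-time test is 26.5% under independence and about 17-25% under the assumed correlations, which is three to five times the nominal 5%.

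This rests on three assumptions: the any-one reading, each test holding its nominal 5%, and correlations that the document does not supply. It does not show that the investigators intend to claim success on any single outcome, nor that an unseen plan lacks an adjustment.

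The sample size rests on the PSQI, which section 2.8.1 lists as secondary. That mismatch is a separate issue and is not settled here.

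**What to change.** Make the change before unblinding and record it as a dated amendment in the protocol and the registry entry. Recruitment began in May 2022 (section 2.1), so this alters the primary outcomes of a running trial and needs that record. Choose one of two routes:

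1. Name one of the listed primary outcomes as the single primary, with one named contrast or visit, and make the others secondary.
2. Keep a short primary family, for example sleep efficiency, ISI and ESS, at one named contrast or visit, tested with Holm's procedure at overall two-sided 0.05.

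Under either route, move time in bed out of the primary set and report it descriptively, and delete the word conservative from section 2.12.

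The first route costs no power through multiplicity. The second lowers power at Holm's strictest step from about 82% to 68% with three outcomes; keeping all six would lower it to 59%. These figures take 35 per arm and borrow the PSQI effect for outcomes that have no effect size in the document, so they show the relative loss and not the trial's actual power.

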## 3. Discussion

The planning of sleep interventions for athlete populations is different than for other populations, such as as neurological or psychological populations. It requires special considerations for the following reasons. First, the prevalence of sleep disturbances in athletes is high. Second, sleep medication can negatively influence sports performance by impairing the efficacy of resistance, prolonged endurance, and high-intensity exercises [35]. Finally, the current interventions for sleep require a long time and commitment, making adherence challenging [1]. Therefore, we suggest that using a robust intervention method such as tDCS is more feasible for athletes.

This study will assess the effect of bilateral anodal tDCS stimulation specifically over the right and left DLPFCs through small electrodes. The only tDCS study [23] that was conducted for athletes reported that the stimulation was for frontal areas without specifying the targeted areas. The tDCS programs for sleep were generally for the left DLPFC in other populations [19]. The selected tDCS stimulation protocol (bilateral anodal) to improve sleep quality is novel in athletes.

The bilateral anodal tDCS could improve sleep via direct and indirect effects on sleep structures [16]. The right and left prefrontal cortices have important roles in sleep regulation and showed decreased activity in people with poor sleep quality and insomnia [36]. Bilateral DLPFC anodal stimulation might induce the ‘top-down’ pathway of sleep–wake regulation [37]. DLPFC networks generate slow oscillations that are biphasic changes in the membrane potential from a hyperpolarized state (down phase) to a depolarized phase (top phase) (<1 Hz) [38]. Furthermore, tDCS could increase the NREM2 sleep stage and decrease slow wave sleep stage regulation [18]. In addition to the direct effects, the tDCS could improve pain, depression, or anxiety and therefore sleep [16]. To understand the mechanism of improvement, correlation analysis of the changes in objective sleep results with athletes’ characteristics and secondary outcomes at baseline will be conducted.

In this protocol, tDCS parameters of a 1.5-mA intensity in 1 cm^2^ (0.057 mA/cm^2^ in density) for 20 min/session 6 times for 2 weeks will be used. The rationale for using 1.5 mA is to generate slow oscillation in the DLPFCs. The tDCS intensity ranges between 1 and 2 mA in sleep trials [16]. A previous study found that 1.5 mA is more effective than 1 mA in people with poor sleep quality [39]. The current parameters are considered safe based on data of more than 33,200 sessions and 1000 participants [40]. The study concluded that the tDCS protocols at ≤4 mA for ≤40 min had not produced any reports of a serious adverse effect or permanent injury [40].

The current study’s outcome measures include subjective and objective sleep measurements, psychological outcomes, and quality of life, which were not previously examined in athletic participants. A previous study [26] found low correlation between the subjective and objective sleep measures and recommended using subjective and actigraphy sleep measures to comprehensively assess sleep. Therefore, exploring the therapeutic effects of the bilateral anodal tDCS on different sleep parameters, quality of life, and psychological status in the athletic participants with sleep disorders may provide a promising noninvasive tool for athletic sleep disorder management.

## 4. Conclusions

The results of this trial may provide an important advancement and contribution in sleep management among athletes. Because of the high incidence and impact of poor sleep quality among athletes, it is particularly important to explore an effective method for sleep disorder management in athletes. This experiment will provide a new direction in sleep management among athletes.

## Figures and Tables

**Figure 1 jcm-11-05883-f001:**
[figure not shown]
The CONSORT flow diagram of the study procedures. CONSORT = Consolidated Standards of Reporting Trials, tDCS = transcranial direct current stimulation.

**Figure 2 jcm-11-05883-f002:**
[figure not shown]
The tDCS electrode placement. (**A**) Anodal and cathodal stimulation according to the 10−10 system. (**B**) Brain schematic view showing the targeted cortices through the anodal and cathodal brain stimulation.

## Data Availability

The data presented in this study will be available on request from the corresponding author.
